### Outcomes

#### Primary outcomes

The following outcomes will be assessed after 24 months of recruitment, or when the recruitment target of 20 participants is achieved (whichever occurs first):

Overall proportion of potential participants identified who enrolled in the trial, termed the ‘recruitment rate’.‘Potential participants identified’ is defined as those who have direct contact with the research team.Overall proportion of participants achieving ‘good adherence’ (proportion of days covered >80%) during the trial.‘Proportion of days covered’ is defined as the total medication taken during the 8-week trial period as a proportion of the total medication dispensed.Overall proportion of participants who view JAK inhibitor therapy in PPP to be ‘acceptable’.Acceptability will be measured based on responses to the following question at the end of the 8-week treatment period: ‘Overall, how acceptable was taking upadacitinib to you?’A 5-point Likert scale will be used, with answers dichotomised into acceptable (acceptable/completely acceptable) or unacceptable (completely unacceptable/unacceptable/neutral)

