### Study procedures

The full study activities at each visit are outlined in table 3. The patient participant pathway consists of three periods: a screening period, a treatment period and a follow-up period. The screening period is up to a maximum of 3 months. Patients who fail the screening process may be re-screened if clinically appropriate.

**Table 3 T3:** Schedule of trial activities

	Screening (<3 months between screening and baseline)	Treatment period				Follow-up	Safety follow-up
**Allowed visit window:** **+** **3 days**	**Visit 0**	**Visit 1**	**Visit 2**	**Visit 3**	**Visit 4**	**Visit 5**	**Visit 6**
		Baseline	(week 1)	(week 4)	(week 8)	(week 12)	(week 20)
	Study enrolment	Treatment initiation			Treatment end	Study end	
Written informed consent	X						
Inclusion/exclusion eligibility check and sign-off	X	X					
Demographics	X						
Medical history	X	X					
Social history	X						
Family history	X						
PPP history	X						
Clinical phenotyping of disease/concomitant psoriasis	X						
Physical examination	X						
Vital signs*	X	X	X	X	X	X	
PPPASI† (×2: blinded and unblinded assessment)	X	X	X	X	X	X	
Fresh pustule count†	X	X	X	X	X	X	
Total pustule count†	X	X	X	X	X	X	
PPP-IGA† (×2: blinded and unblinded assessment)	X	X	X	X	X	X	
PASI (plaque psoriasis only)	X	X	X	X	X	X	
BSA	X	X	X	X	X	X	
Patient global assessment	X	X	X	X	X	X	
DLQI		X			X	X	
EQ5D-5L		X			X	X	
DOSE-Nonadherence questionnaire			X	X	X		
Photography (palms and soles)		X	X	X	X	X	
CXR‡	X						
T-Spot.TB§	X						
HIV, HBV and HCV	X						
Safety bloods¶**	X^††^	X^††^	X	X	X	X	
bHCG (blood)‡‡	X	X			X	X	
Prescribing and dispensing trial IMP		X		X			
Retrieval of IMP packaging (pill count)				X	X		
Acceptability Questionnaire§§		X				X	
RCT scoping question						X	
Concomitant meds	X	X	X	X	X	X	X
Adverse events monitoring		X	X	X	X	X	X

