**Integrated qualitative study**							
Trial participant interview	X				X		
Trial decliner interview	X						
Healthcare professional interview	Interviews will take place with healthcare professionals throughout the duration of the trial (maximum one interview per healthcare professional)						

* Vital signs include heart rate, blood pressure, oxygen saturations, respiratory rate and temperature.

† Assessed by independent blinded assessor. PPPASI and PPP-IGA were also assessed by a second assessor.

‡ CXR not indicated if participant has had a CXR in the previous 12 months for clinical purposes.

§ T-Spot.TB not indicated for those participants known to have been successfully treated for TB (completed the prescribed treatment courses) as screening test is not clinically indicated. If unsure, please seek specialist advice.

¶ Safety bloods comprise WBC, Hb, platelet count, creatinine, urea, sodium, potassium, bilirubin, aspartate aminotransferase, alanine transaminase, HbA1c and cholesterol.

** CRP to be collected at baseline (visit 1) only.

†† If the time between screening and baseline safety assessment bloods is >4 weeks (ie, for participants washing out for 3 months from biologic therapy) the participant should be asked to attend for additional safety assessment blood tests. If feasible, this should be on the same day as the baseline visit allowing for time to clinically review the results before the first treatment dose (in which case only one set of baseline safety assessment bloods should be taken); however, if not convenient, it should be scheduled within 4 weeks of the baseline visit (these may be taken by their GP). If the participant attends an extra visit for these tests, then they should also go on to complete the full baseline visit, that is, repeat the baseline safety assessment bloods as scheduled.

‡‡ bHCG not indicated or applicable for postmenopausal women.

§§ Acceptability questionnaires will be completed during Visits 1 and 5 for participants not taking part in the integrated qualitative study (qualitative study participants will complete the questionnaires during the interviews).

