bHCG, beta-human chorionic gonadotropin; BSA, body surface area; CXR, chest X ray; DLQI, Dermatology Life Quality Index; EQ5D-5L, European Quality of Life 5 Dimensions 5 Level Version; Hb, haemoglobin; HBV, Hepatitis B virus; HCV, Hepatitis C virus; IMP, investigational medical product; PPP, palmoplantar pustulosis; PP-PASI, Palmoplantar Pustulosis Psoriasis Area and Severity Index; PPP-IGA, Palmoplantar Pustulosis-Investigator Global Assessment; RCT, randomised controlled trial; TB, tuberculosis.

The treatment period (visits 1–4) is 8 weeks. At the start of the treatment period, eligible patient participants will receive upadacitinib, to be administered daily as an oral tablet for 8 weeks. Participants will receive 4 weeks of medication at Visit 1 (baseline) and Visit 3 (week 4).

The follow-up period (visit 5) at week 12 will be used to assess disease relapse off study treatment, follow-up any adverse events and plan for post-trial management of their condition. Participants will also be asked the following question to scope out their views on a future RCT: ‘Would you be interested in participating in a trial similar to this with either a dummy arm or active comparison drug arm in the future?’. A final safety review (visit 6) will be carried out at week 20 to assess for any further adverse events.

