### Integrated qualitative study

Qualitative research will be integrated into the trial to provide fundamental insights into the feasibility and design of a definitive trial. Qualitative interviews will be undertaken in the following three cohorts:

Trial participants: semistructured interviews before and after the 8-week treatment period (up to 20 interviews).Trial decliners: one semistructured interview per trial decliner (up to 10 interviews). Trial decliners are individuals who have been invited to participate in the clinical trial and then declined.Healthcare professionals: one semistructured interview per healthcare professional (up to 10 interviews).

Qualitative interviews will be undertaken by an appropriate, delegated member of the research team. These interviews will be conducted either in person or online via Microsoft Teams, depending on participant preference. Interview topic guides will be used to ensure similar areas are covered with each participant, but will be sufficiently flexible to encourage the interviewees to express their own views about the study. We will aim to interview up to 10 eligible participants in each cohort, or up until data saturation has been reached (no new themes were generated after three sequential participant interviews).

The semistructured interviews will be recorded, transcribed verbatim and thematically analysed.^35^ Transcripts will be reviewed and coded thematically using the NVivo 15 software package, identifying key insights, experiences or opinions. Coded interviews will be reviewed and compared so as to characterise recurrent and/or prioritised ideas about the study and interventions. The perspectives of different participants will be compared and synthesised in this process in order to reflect on similar and different experiences. Analytic codes and themes will be tested and refined as new data are considered. The results will be triangulated with the other study findings to inform recommendations for implementing trial findings and the design of the future definitive RCT. Differences in prospective and retrospective acceptability will be explored via comparison between the pretrial and post-trial interview responses.^36^

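### The primary acceptability item is defined at the end of treatment (week 8), but the visit schedule collects it at week 12 from every participant who is not interviewed

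*Protocol article*

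**What the plan says.** Acceptability is one of the three primary outcomes. The Primary outcomes section states its timing: "Acceptability will be measured based on responses to the following question at the end of the 8-week treatment period". The answer, on a five-point scale, is dichotomised, and Table 2 classes the resulting proportion as non-feasible (<20%), intermediate (20–80%) or feasible (>80%).

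The schedule in Table 3 gives other times. The row "Acceptability Questionnaire" is marked under Visit 1 (baseline) and Visit 5 (week 12), with no mark under Visit 4 (week 8, treatment end). Footnote §§ to that row says in words: "Acceptability questionnaires will be completed during Visits 1 and 5 for participants not taking part in the integrated qualitative study". It adds that "qualitative study participants will complete the questionnaires during the interviews". Table 3 marks the trial participant interview at Visit 0 (screening) and Visit 4.

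The Integrated qualitative study section plans, for trial participants, "semistructured interviews before and after the 8-week treatment period (up to 20 interviews" in total, and states: "We will aim to interview up to 10 eligible participants in each cohort". On Visit 5, the text that follows Table 3 says: "The follow-up period (visit 5) at week 12 will be used to assess disease relapse off study treatment".

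The document does not reconcile these time points or say which answer enters the primary proportion.

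**The concern.** If the schedule is followed, the primary proportion pools two sets of answers. Interviewed participants answer at treatment end, as defined. The others answer four weeks later, off drug, at a visit whose stated purpose includes looking for relapse. A view of the treatment formed at its end may differ from one formed after four weeks without it.

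Participants may choose the trial, the interviews or both (Participant recruitment section), so the time of answering is tied to who was interviewed. It is also tied to setting, inside or outside an interview. The analysis could not separate these influences afterwards.

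At stake is one of the three domains that decide whether a definitive trial goes ahead. An analysis plan cannot repair this, because it cannot supply a week-8 answer that the schedule never asks for.

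**Working it through.** **1. Time points side by side**

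| Source | Who | Post-treatment answer |
|---|---|---|
| Primary outcomes | everyone | week 8 |
| Table 3 row and footnote §§ | not interviewed | Visit 5, week 12 |
| Footnote §§ with the Table 3 interview row | interviewed | Visit 4, week 8 |

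The gap is 12 − 8 = 4 weeks, or 28 days. The visit window in the Data collection and management section is 3 days either side, so it does not bridge the gap. The baseline answers also differ in timing (screening interview against Visit 1), but they do not enter the primary proportion.

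**2. How many answers are affected**

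Up to 20 participant interviews at two each is 20/2 = 10 people, which agrees with the cap of 10 per cohort. With 20 enrolled, at least 20 − 10 = 10 answers (10/20 = 50%) fall at week 12. If interviewing stops early at saturation with k < 10 people, the number is 20 − k, which is larger.

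**3. The plan's own precision figure**

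The plan states no precision for acceptability. The nearest figure is the adherence interval in the Sample size rationale: 75% of 20, 95% CI 51% to 91%. The exact (Clopper-Pearson) interval for 15/20 is 50.9% to 91.3%, so that figure is reproduced. The same method gives 56.3% to 94.3% for 16/20 and 62.1% to 96.8% for 17/20.

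**4. The threshold in counts**

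0.80 × 20 = 16, and feasible requires strictly more than 80%. Hence 16/20 = 80% is intermediate and 17/20 = 85% is feasible. One changed answer separates them.

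**5. Illustration of the consequence**

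The acceptability probabilities here are assumptions, not figures from the document. Let X₈ ~ Bin(10, p₈) be the week-8 answers and X₁₂ ~ Bin(10, p₁₂) the week-12 answers. The chance of being classed feasible is P(X₈ + X₁₂ ≥ 17) under the schedule, and P(Bin(20, p) ≥ 17) if everyone answers at one time.

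| p₈ | p₁₂ | All at week 8 | Scheduled mix | All at week 12 |
|---|---|---|---|---|
| 0.90 | 0.90 | 0.87 | 0.87 | 0.87 |
| 0.90 | 0.80 | 0.87 | 0.65 | 0.41 |
| 0.90 | 0.70 | 0.87 | 0.41 | 0.11 |
| 0.80 | 0.90 | 0.41 | 0.65 | 0.87 |

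If views are stable, the mix changes nothing. If they shift by 10 points, the chance of a feasible result moves by about 0.22 to 0.24, down or up according to the direction.

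**The case against.** The strongest reply is that the effect is unknown and the consequence is cushioned. No figure in the document suggests that acceptability changes between weeks 8 and 12. The direction is open too: relapse off drug could make the treatment look better in retrospect. That one answer separates 17/20 from 16/20 is true of any 80% cut with 20 participants. Intermediate is not failure: Table 2 is applied together with the qualitative findings and steering committee review, and the Acceptability section explains that the wide middle band was chosen because numbers are small. All of this stands. It limits how much harm can be claimed, but does not make the schedule agree with the definition. Nor is the mismatch a damaged table, since footnote §§ repeats the visits in words.

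A reader might infer four stronger points that the document does not support:

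- **On-treatment against off-treatment answers.** Visit 4 is treatment end, the text places the second interview after the treatment period, and the item is worded in the past tense. The supportable contrast is end of treatment against four weeks later.
- **No answer meets the definition.** The interviewed participants' Visit 4 answers do.
- **Spoken against self-completed answers.** Footnote §§ says that interviewees complete the questionnaires during the interviews. It does not say that they answer aloud, nor how the others complete theirs. The setting differs; a difference in mode is not stated.
- **Late recruits' answers are lost.** Outcomes are to be assessed after 24 months "or when the recruitment target of 20 participants is achieved (whichever occurs first"). Read literally, this comes before the last participants reach week 8. At 20/24 = 0.83 recruits per month, that would be 0.83 × 1.84 = 1.5 participants over 8 weeks, or 0.83 × 4.84 = 4.0 with the maximum three-month screening added. But every participant is scheduled to week 20 and the outcome itself is defined after eight weeks, so the sentence more naturally marks the end of recruitment. Nothing says that later data are dropped.

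**Conclusion.** The contradiction is real and concerns a primary outcome with a progression threshold. As scheduled, at least 10 of 20 acceptability answers would be taken four weeks after the defined time point, and which participants these are follows non-random interview participation. The count assumes that 20 are enrolled and no more than 10 are interviewed.

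One changed answer can move a result from feasible to intermediate. Whether any answer would change, and in which direction, cannot be derived from the document, so no bias in a particular direction is claimed. The probabilities in the illustration show sensitivity under assumed values only. The case for correction rests on the mismatch itself and on the fact that uncollected week-8 answers cannot be recovered.

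**What to change.** Add the acceptability item at Visit 4 in Table 3 for every participant and revise footnote §§ to match. Preferably, have everyone complete it in the same way and, for interviewees, before the interview begins. State that this answer alone feeds the primary outcome and the Table 2 criterion, and keep the Visit 5 answer as a supplementary off-treatment reading.

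The cost is a small amendment: one table entry, one footnote and one short questionnaire at a visit that already takes place. Recruitment was planned to start in November 2024, so the amendment should also say how participants who have already passed Visit 4 without the item will be counted.

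As an optional tidy-up, the Primary outcomes section could state that adherence and acceptability are assessed once the last recruited participant has completed week 8.

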#### Secondary outcomes

The following outcomes will be assessed after 24 months of recruitment, or when the recruitment target of 20 participants is achieved (whichever occurs first):

Total number of potential identified participants who have contact with the research team.Speed of participant identification (participants identified/month).Speed of participant recruitment (participants identified/month).Total number of ineligible participants.Reasons for ineligibility.Recruitment of 20 participants within 24 months.Overall mean change in Palmoplantar Pustulosis-Psoriasis Area and Severity Index (PP-PASI) over the 8-week treatment period, adjusted for baseline PP-PASI.^22^Placebo control data from the APRICOT (2015–2020, n=31 with complete data) will be used as a comparator.

The following outcome is assessed at the end of each phase of the QRI approach (new phase for every 20 eligible patient participants approached throughout the trial):

Change in recruitment rate with each phase of the QRI approach.

#### Exploratory outcomes

The following outcomes are assessed after 24 months of recruitment, or when the recruitment target of 20 participants is achieved (whichever occurs first):

Evaluation of trial recruitment diversity and inclusion.Participant demographics will include age, sex, ethnicity and socioeconomic background.Accuracy of disease severity assessments of photographs compared to in-person assessments.PP-PASI and Palmoplantar Pustulosis-Investigator Global Assessment (PPP-IGA) grading of photographs will be compared with in-person disease severity assessments.Overall mean change in total pustule count over the 8-week treatment period, compared to baseline adjusted for baseline total pustule count.Placebo control data from the APRICOT (2015–2020, n=31 with complete data) will be used as a comparator.Overall mean change in fresh pustule count over the 8-week treatment period, compared to baseline adjusted for baseline fresh pustule count.Placebo control data from the APRICOT (2015–2020, n=31 with complete data) will be used as a comparator.Overall proportion of participants achieving clearance of PPP over the 8-week treatment period.Clearance will be defined as a PPP-IGA of 0/1.Placebo control data from the APRICOT (2015–2020, n=31 with complete data) will be used as a comparator.Overall mean change in chronic plaque psoriasis severity (if applicable) over the 8-week treatment period, adjusted for baseline chronic plaque psoriasis severity.Severity will be assessed using the PASI.^23^Placebo control data from the APRICOT (2015–2020, n=16 with complete data) will be used as a comparator.Overall mean change in participants’ symptoms and quality of life over the 8-week treatment period, adjusted for baseline. Dermatology Life Quality Index, Patient Global Assessment and European Quality of Life 5 Dimensions 5 Level Version (EQ5D-5L) will be used to assess participants’ symptoms and quality of lifePlacebo control data from the APRICOT (2015–2020, n=31 with complete data) will be used as a comparator.Overall proportion of participants achieving a 50% reduction in PP-PASI score (PPPASI50) over the 8-week treatment period, compared to baseline (visit 1).Placebo control data from the APRICOT (2015–2020, n=31 with complete data) will be used as a comparator.

### Adverse events monitoring

Adverse events will be tabulated and described for all subjects who received at least one dose of study medication. Adverse events will be summarised by event type, including information on the number with at least one event and the number of events to account for recurrent events.

### Sample size rationale

We will aim to recruit 20 participants, in keeping with other published feasibility studies.^24 25^ Over a 24-month recruitment period, we anticipate approaching a total of around 100 potentially eligible individuals. Based on previous experience, we anticipate that the actual recruitment rate would be no less than 20%, so this would provide us with at least 20 participants.

With 100 approached participants, if 20 (20%) are recruited into the trial, this would allow us to estimate the 95% CI for the recruitment rate with precision of at least ±8%. Assuming 75% of participants adhere to treatment at least 80% of the time (as observed in APRICOT), a sample size of 20 participants would allow us to estimate ≥80% treatment adherence with a 95% CI: 51% to 91%. With 20 participants on treatment, JAKPPPOT will estimate a PPPASI50 in the JAK inhibitor arm with precision of at least ±3.43 PP-PASI points. This is based on figures derived from the APRICOT (mean baseline PP-PASI: 17.8; SD for the PP-PASI change at 8 weeks in active arm: 7.32).^16^ A PPPASI50 is an outcome that has been analysed as a primary/secondary endpoint in several PPP trials and was described as ‘treatment success’ during patient and public involvement (PPI) discussions with people with PPP.^26^ The PP-PASI reduction in the treatment arm will inform the sample size calculation for a larger definitive trial.

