### Progression criteria and rationale

Progression criteria have been outlined to determine whether it is appropriate to progress to a subsequent adequately powered RCT, shown in table 2. Findings from the primary and secondary quantitative outcomes will be incorporated with the qualitative findings to inform decisions regarding an ‘intermediate’ results in any domain (ie, upgrade to feasible or downgrade to non-feasible). All recommendations will be reviewed by the trial steering committee (TSC). For criteria judged to be intermediate or non-feasible, the study team will examine the likely causes and consider whether a mitigation strategy could be successfully implemented.

**Table 2 T2:** Progression criteria for the JAKPPPOT trial

Domain	Non-feasible	Intermediate	Feasible
Recruitment: proportion of potential participants identified who enrolled in the trial	<20%	20–40%	>40%
Adherence: proportion of participants achieving ‘Good’ adherence (>80% of medication taken as prescribed)	<20%	20–80%	>80%
Acceptability: proportion of participants who view JAK inhibitor therapy in PPP to be ‘acceptable’	<20%	20–80%	>80%

JAK, Janus kinase; JAKPPPOT, Janus kinase inhibitors in palmoplantar pustulosis: a mixed-methods feasibility; PPP, palmoplantar pustulosis.

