### Recruitment

A low recruitment rate is assumed, in line with the APRICOT study (17% overall recruitment rate).^16^ Factors in favour of a higher recruitment rate than the APRICOT are the single-arm trial design and the use of an oral tablet medication versus a daily subcutaneous injection with a high burden of injection site reactions. Factors negatively impacting recruitment are that this is a feasibility study rather than an efficacy study, there is no associated open-label extension and the potential side effect profile of upadacitinib. Optimisation strategies will be implemented through the trial to improve recruitment.

Secondary quantitative outcomes will be incorporated into the feasibility assessment, for example, failure to recruit 20 participants within 24 months would be an indicator of non-feasibility. If recruitment cannot be achieved in the context of an open-label trial, it is strong evidence against the feasibility of an adequately powered RCT.

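### The sample size rests on a recruitment rate of at least 20%, but the Recruitment section assumes about 17%, at which roughly 100 approaches yield 17 expected participants and a 25% chance of reaching 20

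*Protocol article*

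**What the plan says.** All of this is in the protocol article.

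- **Sample size rationale.** The target is 20: "We will aim to recruit 20 participants, in keeping with other published feasibility studies". The number approached is given as: "Over a 24-month recruitment period, we anticipate approaching a total of around 100 potentially eligible individuals". The rate is then set as a minimum: "we anticipate that the actual recruitment rate would be no less than 20%, so this would provide us with at least 20 participants". The only support offered is previous experience.
- **Recruitment** (under Progression criteria and rationale). "A low recruitment rate is assumed, in line with the APRICOT study (17% overall recruitment rate"). Reasons follow why the rate might be higher than in APRICOT (single arm, oral tablet) and why it might be lower (feasibility aim, no open-label extension, side-effect profile). Optimisation during the trial is also mentioned. No net figure is given.
- **Table 2.** The row "Recruitment: proportion of potential participants identified who enrolled in the trial" is non-feasible below 20%, intermediate from 20% to 40%, and feasible above 40%.
- **Primary outcomes.** The denominator is people in direct contact with the research team.

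**The concern.** A rate of 17% lies below a floor of 20%, so the two sections cannot both be the planning assumption. The one prior rate that the article gives is 17%, and it falls inside the trial's own non-feasible band.

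Two things depend on this. First, the figure of 20 participants carries the stated precision for adherence and for PP-PASI; with 17 participants both are weaker. Second, the recruitment rate is a primary outcome and feeds the decision on a definitive trial. Because the lower cut equals the planning floor, recruitment exactly as planned (20 of 100) sits on the boundary. A reader of Table 2 is not told how likely each verdict is under the rates that the protocol itself names.

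**Working it through.** **Inputs.** Target 20, about 100 approached, and a rate of at least 20% (Sample size rationale); 17% (Recruitment); cuts at 20% and 40% (Table 2); stop at 20 recruits or 24 months (Study design); SD of PP-PASI change 7.32 and adherence 75% (Sample size rationale). I take 100 as the number of contacts and treat enrolments as independent.

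**1. The plan's own figures reproduce.**
- Recruits: 100 × 0.20 = 20.
- Precision of the rate: 1.96 × √(0.20 × 0.80 / 100) = 0.0784, so ±7.84 points, stated as ±8.
- PP-PASI at n = 20: 2.093 × 7.32 / √20 = 3.43, as stated.
- Adherence 15/20: exact 95% CI 51% to 91%, as stated.

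**2. The same plan at 17%.**
- Expected recruits: 100 × 0.17 = 17. The 2.5 and 97.5 percentiles of Binomial(100, 0.17) are 10 and 25.
- P(X ≥ 20) = 0.248.
- Mean contacts needed for 20 recruits: 20 / 0.17 = 117.6, about 118.
- Smallest number of contacts with P(X ≥ 20) of at least 80%: 137 (0.804; 136 gives 0.793).

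**3. Precision if 17 are recruited.**
- PP-PASI: 2.120 × 7.32 / √17 = ±3.76.
- Adherence: 0.75 × 17 = 12.75, so take 13/17; exact 95% CI 50% to 93%.

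**4. Recruitment verdicts with 100 contacts available.** Non-feasible means P(X ≤ 19) in 100. Because recruitment stops at 20, a rate above 40% at full recruitment requires the 20th recruit by the 49th contact, that is P(X ≥ 20) in 49. Intermediate is the remainder.

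| True rate | Non-feasible (<20%) | Intermediate (20–40%) | Feasible directly (>40%) |
|---|---|---|---|
| 17% | 75.2% | 24.8% | <0.1% |
| 20% | 46.0% | 53.9% | 0.07% |
| 22% | 27.8% | 72.0% | 0.2% |
| 25% | 10.0% | 89.0% | 1.1% |

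**The case against.** The strongest reply is that the two rates need not conflict. The 17% is APRICOT's rate, the protocol gives reasons why this trial may do better, and 20% is offered as a minimum. The bases may also differ: the sample-size section counts potentially eligible people approached, the primary outcome counts direct contacts, and the denominator behind the 17% is not given. This stands in part. A rate of 20% or more is possible, and the risk falls quickly above it. But the text says that a low rate is assumed in line with 17%, gives no net effect, and does not put the figures on one base.

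It is also fair to say that a 75% chance of non-feasible at a true 17% is correct classification: 17% is below the trial's own cut. That is right. The fault is in promising 20 participants, not in the scoring.

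Four stronger readings are tempting, and the document does not support them.

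- **That the trial cannot be scored feasible.** The small figures in the last column cover only the direct route. Progression criteria and rationale allows an intermediate result to be upgraded to feasible.
- **That the verdict is a coin toss.** This is true only near a true 20%.
- **That the ±8% is wrong.** It is stated for 20 recruited out of 100, and it reproduces.
- **That the two recruitment criteria contradict each other.** The article says that "failure to recruit 20 participants within 24 months would be an indicator of non-feasibility". Recruiting 20 in time is a secondary outcome and is nowhere made sufficient for feasibility. With exactly 100 contacts available, the two criteria always agree.

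**Conclusion.** The point holds as an inconsistency in the planning figures. The sample-size section relies on at least 20 participants from about 100 approached; the Recruitment section's 17% supports 17 expected, with a 25% chance of 20. The loss of precision at 17 participants is modest (PP-PASI ±3.76 against ±3.43). The chance of an observed rate in the non-feasible band is 75% at a true 17% and still 46% at the planning floor, falling to 10% at 25%.

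The consequence is limited. A non-feasible result leads to an examination of causes and possible mitigation, with recommendations reviewed by the trial steering committee; it does not stop the programme automatically. The figures assume 100 contacts, independent enrolments, and that 17% and 20% refer to the same denominator, which the article does not establish.

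**What to change.** 1. State one planning rate on the denominator defined under Primary outcomes: people in direct contact with the research team.
2. Either justify the gain from 17% to at least 20%, or replace the promise of at least 20 participants with the figures at 17%: 17 expected from 100 contacts (95% range 10 to 25), a 25% chance of 20, about 118 contacts needed on average and 137 for an 80% chance. In the second case, give precision at 17 participants: PP-PASI ±3.76, and adherence 13/17 with exact 95% CI 50% to 93%.
3. Beside Table 2, give the probability of each recruitment verdict at true rates of 17%, 20% and 25%, as in the table above.

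I would not add a rule that scores a rate below 20% as intermediate once 20 have been recruited. With 100 contacts it can never apply, so the 46% and 75% would not change. With more contacts it would loosen a primary progression criterion without limit: 20 from 300 contacts, or 6.7%, would count as intermediate.

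The cost is a few sentences in the sample-size section and a note to Table 2. No extra patients and no change to the cuts are needed; some stated figures become less favourable.
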